## Volumetric MRI in Preterm Infants with WM Injury Studied at Term

In a first study to apply these techniques to study effects of brain injury 3-D MRI volumetric techniques were used to evaluate the effect on subsequent brain development of early WM injury in premature infants. Studies were done at 40 weeks postconceptional age in a total of 34 infants. In the premature infants with preceding WM injury, the volume of total gray matter, cortical gray matter and myelinated WM at term was

*Table. Quantitative 3D-MRI Volumes of Cerebral Tissues at Term in Premature Infants with Evidence of PVL, Premature Infants with no Evidence of PVL, and Healthy Term Infants*

|                               | Premature with PVL,
at Term (n = 10) | Premature with No
PVL, at Term (n = 10) | Normal Term
(n = 14) | p (ANOVA, Pairwise
Multiple Comparisons) |
|-------------------------------|-----------------------------------------|--------------------------------------------|-------------------------|---------------------------------------------|
| Cerebral cortical gray matter | 157.5 ± 41.5                            | 211.7 ± 25.4                               | 218.8 ± 21.3            | <0.001                                      |
| Basal ganglia/thalamus        | 22.5 ± 7.6                              | 29.7 ± 14.2                                | 24.7 ± 9.1              | NS                                          |
| Total gray matter             | 180.1 ± 49.5                            | 241 ± 39.6                                 | 243 ± 30.4              | 0.001                                       |
| Myelinated white matter       | 14.5 ± 4.6                              | 23.1 ± 6.9                                 | 27.6 ± 10.3             | 0.002                                       |
| Unmyelinated white matter     | 178.3 ± 33.9                            | 212.8 ± 28.4                               | 200.3 ± 32.9            | NS                                          |
| Total white matter            | 192.8 ± 38.9                            | 235.9 ± 35.3                               | 227.9 ± 43.7            | NS                                          |
| CSF                           | 64.5 ± 15.2                             | 52.0 ± 24.1                                | 32.9 ± 13.5             | <0.001                                      |

Data are volumes in milliliters and are mean ± SD values.

3D-MRI = three-dimensional magnetic resonance imaging; PVL = periventricular leukomalacia; ANOVA = analysis of variance; CSF = cerebrospinal fluid.

significantly lower than in both the premature infants without prior WM injury and the infants born at term^7. These data support the hypothesis that injury to the developing WM during the critical period of WM maturation will result in impairment

not only of the very early phases of myelination, but also will alter subsequent cortical development, detectable by volumetric MRI at term.

## Diffusion Weighted Imaging (DWI) in newborns

The DWI technique measures the diffusivity of brain water and is quantitatively expressed as the apparent diffusion coefficient (ADC). Experience with the DWI technique has been confined largely to the study of stroke, primarily in adults, but also to some extent in term newborns. ADC

changes precede the appearance of abnormalities on conventional T2-weighted MRI for ischemic injury. However, until recently, normative data had been unavailable for the premature brain, limiting the ability to identify ischemic injury in the newborn by this technique.

To determine the normal developmental changes of the ADC in cerebral WM, DWI studies in preterm and term newborns (GA from 28 to 40 weeks) were performed within the first two weeks of life. The data showed important changes in the quantitative measurements of water diffusion in the developing brain. Specifically, there was a marked decline in the ADC values in the central WM over this gestational age range, indicative of a progressive decrease in water diffusion. These findings provided new insights into the implications of changes in ADC values with WM development and will be used as a baseline for the data collected in the current study.

To provide insight into the nature of the microstructural developmental events associated with the decrease of the ADC described above, diffusion tensor analysis can be used to determine diffusion anisotropy, a measure of the directionality of diffusion in cerebral WM. In this study on developmental changes of the DTI parameters relative anisotropy (RA) showed a striking increase in cerebral WM from 28 to 40 weeks.

#### **7.4.2 Additional Objectives for the MRI**

To determine whether early rhEPO treatment will improve neurostructural development at term assessed as (a) increased myelinated white matter volume (by quantitative volumetric MRI) (b) improved microstructural development (by diffusion tensor MRI) of cerebral white matter and (c) increased cortical and subcortical (basal ganglia) gray matter volume (by quantitative volumetric MRI).

To assess whether modern MR-imaging techniques, e.g. diffusion tensor imaging (DTI), and MR spectroscopy (MRS) can predict neurological abnormalities in preterm infants.

#### **7.4.3 Procedure of MRI examination**

Infants will be studied at 40 weeks gestation (near the expected term) during natural sleep at the Center for magnetic resonance, Children's Hospital Zurich and Geneva. The parents will bring their infants to the center, feed them and let them fall asleep. The infants will then be fixated on a table with heated mattress and brought to the magnet. If they wake up, they will get a sweet solution with a pacifier. If they can not be calmed, the study will be terminated.

#### **7.4.4 Analysis of MRI data**

In Zurich MRI data will be stored on CD and sent to Geneva by [name]. Volumetric assessment to demonstrate the effect of EPO (Objective 1) will be done by [name], Geneva. Sophisticated DTI and fibre tracking methods will be used by [name] to predict neurological outcome (objective 2).

#### **7.4.5 Information of parents**

The parents will be informed about the planned MRI examination before the infant is discharged home and have to give written consent. If there is a medical indication for the MRI examination (for example pathological cerebral ultrasound finding) they will only have to agree that the results are also analysed for the Epo-trial.

If the parents do not want an MRI examination, the infant will stay in the study cohort as the main outcome is developmental status at 24 months corrected for prematurity.

The results of the MRI-analysis will be explained to the parents by [name] or [name]

## 7.5 Individual Withdrawal Criteria

A patient will be withdrawn from the study when one of the following criteria is fulfilled:

1. violation of the study protocol
2. intolerable side effects
3. any conditions that might jeopardize the patient's health if they were to continue in the study

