| Primary Objective           | Mental development at 24 months (Bayley II)                                                                                                                                                                                                                                                                                                                                                                                                                                                                                                                                                                                 |
| Secondary Objectives        | 
 
1. Incidence of intracranial haemorrhage
 
2. white matter disease (periventricular leucomalacia)
 
3. septicaemia
 
4. necrotising enterocolitis
 
5. persistent ductus arteriosus (PDA)
 
6. bronchopulmonary dysplasia
 
7. retinopathy
 
8. Length of stay in hospital
 
9. Cerebral volume at 40 postmenstrual weeks (MRI)
 
10. Weight, length and head circumference at 40 postmenstrual weeks and 24 months after term
 
11. Incidence of visual, hearing and motor impairment at 24 months
 
 |
| Inclusion Criteria          | 
 
1. Infants born between 260/7 and 316/7 gestational weeks
 
2. Postnatal age less than 3 hours
 
3. Informed parental consent (preferably obtained before birth)
 
                                                                                                                                                                                                                                                                                                                                                                      |

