#### **4.3 Study duration**

The study is scheduled to begin on 01 January 2006. The in-hospital phase of the study will last minimum 8 weeks, maximum 14 weeks (until 40 completed weeks of gestation). All patients will

be followed up for developmental outcome at 24 months after term and at five years. Therefore the whole study will last five years for each participating child.

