### **7.2 Study-related Procedures**

Within the study, the following tests will be performed routinely (medically indicated tests and examinations):

1. Minimal electronic monitoring includes heart rate (or pulse rate) with recommended alarm limits at 90 and 180 beats per minute, arterial saturation (pulse oximetry) with recommended alarm limits at 85% and 95%.
2. Arterial blood pressure will be monitored continuously if there is an indwelling arterial line and intermittently by oscillometric measurement at least every 8 hours during the first 7 days.
3. In selected infants cerebral perfusion and oxygenation will be monitored with near infrared spectroscopy (NIRS) 10 min before until 60 minutes after first epo/placebo dose (optional).
4. Serial cerebral ultrasound assessment will be carried out on day 1 and 7 to 10 and then every 14 days until 360/7 weeks postmenstrual age (or at discharge if discharged before) to detect intracranial haemorrhage graded after Papile, ventricular dilatation and white matter disease (periventricular echodensities at 7 to 10 days and periventricular leukomalacia at 36 postmenstrual weeks). The final cerebral ultrasound includes the worst findings in that hospitalisation.
5. Both eyes are examined by an ophthalmologist to detect retinopathy of prematurity (ROP). The severity of ROP will be graded according to the international classification of ROP.
6. Necrotising enterocolitis is diagnosed by clinical signs (abdominal distension, bilious aspirates, and/or bloody stools) and either pneumatosis intestinalis, hepatobiliary gas, or free intraperitoneal air on abdominal x-ray or at laparotomy. Severity of enterocolitis will be graded according to presence and severity of complications.
7. Septicaemia is diagnosed by clear clinical, radiological, or histological evidence of infection and at least one microbiologically relevant positive blood culture.
8. Persistent ductus arteriosus (PDA) is diagnosed clinically or with echocardiography and documented only if drug treatment (indomethacin or ibuprofen) or surgical ligation is required.
9. Weight and head circumference are recorded at birth, at 7 to 10 days, at 360/7 postmenstrual weeks, at 24 months and 5 years corrected age.
10. Optional MRI examination of the head will be performed at the age of 40 (+/- 4 weeks) postmenstrual weeks. Data will be analysed by Prof. [name], Geneva.

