## 7.6 Individual End of the Study

The end of the study for each patient will be death, discharge home or gestational age of 40 (+4 weeks) completed weeks.

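### Section 7.5 withdraws infants from the study after post-randomisation events without keeping their 24-month assessment, and sections 7.5 and 7.6 do not fit the follow-up promised in 4.3 and 7.8

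*Protocol*

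**What the plan says.** Section 7.5 opens with "A patient will be withdrawn from the study when one of the following criteria is fulfilled". It then lists three reasons: "violation of the study protocol", "intolerable side effects", and any condition that could endanger the infant if the study went on. It does not separate stopping study drug from leaving the study, and it does not mention later assessments.

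Section 7.6 adds: "The end of the study for each patient will be death, discharge home or gestational age of 40 (+4 weeks) completed weeks".

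Other parts of the protocol point the other way:

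- Section 4.3 says that all patients will "be followed up for developmental outcome at 24 months after term and at five years", and that the study lasts five years for each child.
- Section 7.8 describes the Bayley II examination at 24 months corrected age and further tests at 5 years. The diagram in 1.7 lists the Bayley at its 24-month assessment (A5).
- The synopsis names mental development at 24 months as the primary objective. It labels the period to the 40th week as the clinical part and adds 24 months of follow-up.
- Section 7.4.5 keeps infants without an MRI in the cohort, because the main outcome is measured at 24 months.

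On growth, the synopsis lists "Weight, length and head circumference at 40 postmenstrual weeks and 24 months after term" as a secondary objective. Section 7.2 item 9 begins "Weight and head circumference are recorded at birth, at 7 to 10 days" and continues with 36 0/7 weeks, 24 months and 5 years.

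**The concern.** The withdrawal rule is mandatory, and it removes the infant from the study as a whole. Each trigger occurs after randomisation. Side effects and health risk may depend on the treatment given, and protocol violation is not defined. The last dose is scheduled at 36 to 42 hours. After that no study drug remains to be stopped, so a withdrawal can then only cost outcome data.

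If a centre reads 7.5 literally and does not recall the infant at 24 months, the primary outcome is missing for a group selected by events after randomisation. If that group differs between arms in size or severity, the comparison of MDI is biased. An analysis plan can define who is analysed, but it cannot supply a Bayley score that was never obtained.

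Section 7.6 makes this worse. It gives a centre no signal that a withdrawn infant is expected back, because it ends every infant's study long before the primary endpoint.

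**Working it through.** **1. The plan's own sample size.** The synopsis gives 176 per group, two-sided alpha 0.05 and power 0.80. Section 7.8 gives an SD of 15 for the MDI. The readable text gives no target difference (the diagram in 9.1 is not shown), so it has to be back-solved:

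- Detectable difference = 15 × √(2/176) × (1.960 + 0.842) = 4.48 points.
- With an assumed 4.5 points (0.3 SD), n = 2 × (1.960 + 0.842)² × 15² / 4.5², which rounds up to 175 per group. The t-test version gives 175.4, so 176.

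The figure of 176 is plausible and is not disputed. The 4.5 points are an inference, not a protocol figure.

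**2. The reserve.** 2 × 176 = 352, 420 − 352 = 68, and 68/420 = 16.2%. These 68 infants must cover deaths, loss to follow-up and withdrawals together. With 4.5 points and SD 15 assumed, power by total loss is:

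| Total loss | Power |
|---|---|
| 0% | 86.7% |
| 16.2% | 80.3% |
| 20% | 78.5% |
| 25% | 75.9% |
| 30% | 73.0% |

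**3. Bias from selective withdrawal.** The protocol gives no withdrawal rates, so these inputs are assumptions. Let w1 and w0 be the proportions withdrawn and not assessed in the two arms. Let g be the number of MDI points by which those infants score below the retained ones, with the same g in both arms. The full-arm mean is the retained mean minus w × g, so the bias in the difference is (w1 − w0) × g. With SE = 15 × √(2/176) = 1.60, the type I error is 1 − [Φ(1.96 − bias/SE) − Φ(−1.96 − bias/SE)].

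| w1 v w0 | g | Bias (points) | Share of 4.5 | Two-sided type I error |
|---|---|---|---|---|
| 5% v 5% | 7.5 or 15 | 0 | 0% | 0.050 |
| 5% v 2% | 7.5 | 0.23 | 5% | 0.052 |
| 5% v 2% | 15 | 0.45 | 10% | 0.059 |
| 10% v 5% | 7.5 | 0.38 | 8% | 0.056 |
| 10% v 5% | 15 | 0.75 | 17% | 0.076 |
| 10% v 2% | 7.5 | 0.60 | 13% | 0.066 |
| 10% v 2% | 15 | 1.20 | 27% | 0.117 |

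The bias favours the arm that loses more of its low-scoring infants.

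**4. The passages side by side.** Section 7.6 ends the study at death, discharge or 40 (+4) weeks. Section 4.3 gives five years per child, and the primary endpoint falls at 24 months. Taken literally these cannot all hold. The synopsis label for the period to the 40th week suggests that 7.6 describes the in-hospital part.

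**5. Growth, a separate matter.** The synopsis sets the neonatal time point at 40 weeks. Sections 7.2 item 9 and 10.2 record weight and head circumference at 36 0/7 weeks. Neither names length.

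**The case against.** The best defence is section 4.3, which extends follow-up to all patients without exception. On that reading a withdrawn infant would still be seen at 24 months. This carries weight: the protocol's intention is probably full follow-up, and the fault is a conflict between 4.3 and 7.5. But 7.5 is the rule a centre will consult when the event happens, and it is silent there. Section 7.4.5 shows that the protocol states retention where it means it, and 7.9 treats withdrawal from the study as a real event that can lead to deblinding.

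Several stronger readings are tempting and are not supported:

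- *Section 7.6 abandons the primary endpoint or breaks the randomised comparison.* The synopsis, 4.3, 7.4.5 and 7.8 all show that 24-month follow-up is planned. A fixed milestone also applies to both arms alike and would not by itself unbalance them.
- *The protocol fails to say that infants are analysed as randomised.* That may properly stand in an analysis plan, which is not at hand.
- *All safety counts are biased.* Section 8.5 has each adverse event documented with onset, end, measures taken and further course, so the event that prompts a withdrawal is itself recorded.
- *Only 26 survivors can be lost.* This applies the 90% survival quoted in the introduction: 420 × 0.9 = 378, and 378 − 352 = 26 (6.9% of 378). That figure describes very preterm infants in general, whereas this trial excludes palliative care and severe malformations.
- *The growth mismatch follows from 7.5 or 7.6, or length is recorded nowhere.* It does not follow from either section, and the diagram in 1.7 lists unspecified growth at 36 weeks and at 24 months.

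**Conclusion.** The point stands for 7.5. As written, it can cause selective loss of the primary outcome and can bias the comparison. Whether it does depends on how many infants are withdrawn and whether their number or severity differs by arm, and the protocol gives no basis for estimating either. The bias is zero with equal withdrawal and an equal deficit in both arms. It is about 0.2 to 1.2 MDI points under the assumed imbalances of 3 to 8 percentage points and the assumed deficit of 7.5 to 15 points. The share of the detectable difference (5% to 27%) also rests on the back-solved 4.5 points. The firm figure is the reserve of 68 infants (16.2%), on which every unassessed infant draws.

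For 7.6 the finding is an internal contradiction to be reconciled, most likely a matter of labelling. The growth time point is a separate, minor mismatch. The 7.5 wording deserves priority because outcomes never collected cannot be restored at analysis.

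**What to change.** - **Section 7.5:** add that an infant who meets any of the criteria stays in follow-up, including the 24-month assessment, unless the parents withdraw consent. Leave the clinical criteria and any decision about study drug as they are.
- **Section 7.6:** reconcile it with 4.3 and 7.8 by calling discharge or 40 (+4) weeks the end of the in-hospital phase.
- **Growth (minor, separate):** align the synopsis endpoint with the data collected. Weight and head circumference are recorded at 36 0/7 weeks, not 40. State where length is recorded if it is to remain part of the endpoint.

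The cost is a wording amendment and 24-month visits for the few infants who might otherwise be dropped.

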## 7.6 Individual End of the Study

The end of the study for each patient will be death, discharge home or gestational age of 40 (+4 weeks) completed weeks.

## 7.7 Patient's consent, information and data protection declaration

As this study involves paediatric patients, the parents will receive information on the study, and give their informed consent for its implementation as the child's legal agents. A data protection declaration will have to be provided for them to sign.

## 7.8 Follow up Study

The follow up study should be based on the assessment of developmental function and handicaps at 24 months as well as 5 years corrected age.

Assessment at 24 months corrected age uses the Bayley Scales of Infant Development (BSID-II). At the same examination the presence or absence of impairment of motor function (cerebral palsy) and neurosensory function (blindness or deafness) will be assessed.

The BSID-II is well standardised, reliable and valid, and one of the most widely used psychometric tests. The MDI scores have a mean of 100 and a SD of 15. This test will allow to detect subtle deviations in cognition. A previously used classification scheme will be used to code the severity of disability (nil, mild, moderate, severe).

Gross motor function will be classified as described by Palisano and used in the ongoing caffeine trial. Blindness will be defined as corrected visual acuity of less than 20/200. Deafness will be defined as hearing loss requiring amplification.

BSID-II has been used by several centres since many years and has been accepted as the standard in the Swiss Neonatal Network together with a neurological examination focusing on gross motor function. All assessments must be performed by trained and experienced examiners.

At 5 years corrected age cognitive development will be assessed with a reliable and validated test (K-ABC II). A standardised neurological, visual and hearing examination will be performed. These tests will be done by trained psychologists or physicians in each centre. The parents will fill in a questionnaire on the child health status and behaviour.

Socioeconomic status will be calculated according to Largo by means of a six-point score of both paternal occupation and maternal education. The lowest possible SES score is 1, the highest 12. Socioeconomic status has been shown to affect cognitive development and therefore is an important confounder, which should be balanced in the EPO group and the placebo group.

The International Classification of Impairments, Disabilities, and Handicaps distinguishes between consequences of diseases and disorders at the level of the body (impairment), the person (disability or limitation of functional activity), and the person as a social being (handicap or limitation of participation in society). In the 24 months assessment we will focus on "disability", in the 5 years assessment we will also include "handicap".

## 7.9 Randomisation and Deblinding

The study is randomised on a double-blind basis. This means that the attending investigators do not know whether they are using the placebo or the verum. Randomisation is performed on the basis of randomisation lists (see 4.2).

In the event that deblinding should be required subsequent to an individual patient's withdrawal from the study, this will be possible by immediate notification of the pharmacy responsible for the study centres, with specification of the centre and randomisation number, within 24 hours.

In the event of deblinding, the Principal Investigator has to be notified within a period of 24 hours. The PI will then take charge of further reporting as required by the GCP guidelines.

